
### Plans to promote participant retention and complete follow-up {18b}

Multiple strategies are used to retain participants over the duration of the study, including (1) providing reminders (e.g., calls, texts) before study data collection visits; (2) limiting participant burden by scheduling data collection study visits when participants are already attending the SUD treatment center; (3) using limited release of medical information forms for EMR abstraction; (4) providing incentives after completion of data collection visits; (5) paying for car ride services (e.g., Uber) and providing parking vouchers to nearby parking garages so participants can park during study visits; (6) collecting contact information of friends and family members who are likely to know the location of subjects should they be temporarily out of contact; and (7) sharing information about the study with staff and providers across hospital departments (e.g., Neonatology, General Pediatrics, Ob/Gyn). In addition, our approach to analyzing the data will allow us to include subjects in analyses who provide partial data due to premature study dropout. Comparisons between study subjects who are retained and who drop out will be conducted to determine biases and non-random patterns of study attrition.

### Data management {19}

Data will be collected primarily using paper-based forms. Research staff will be responsible for entering data from all completed paper form into a secure Research Electronic Data Capture (REDCap) database. Data quality validation with inbuilt quality checks will be programmed into REDCap.

### Confidentiality {27}

All participants will be assigned an anonymous study identification number at enrollment. Study IDs will be used on all instrumentation and will be linked to an individual’s identifying information by a master study key which will be maintained in hard copy locked in the principal investigator’s office. All hard copies of study files as well as videotapes of the recorded play sessions and audiotapes of the interview sessions and focus group discussions will be kept in locked cabinets in research personnel office. Data collection instruments (e.g., questionnaires, EMR abstraction tools), coded video data, and transcripts will omit names and identifiers that could potentially identify the participants. All electronic data files will be saved on a University password-protected, encrypted computer and be backed up daily. Documentation of data management procedures will be carefully maintained. No results will ever be reported in a personally identifiable manner.

Each participant randomized to group WCC will have the opportunity to privately discuss any concerns about her child with the pediatrician before the group visit begins. The group WCC model of care is designed to promote greater breadth and depth of discussion, as well as increased focus on maternal wellness and social determinants of health. Therefore, it is possible that group discussion may bring forth sensitive topics, for example, intimate partner violence that could cause psychological distress for participants. Prior to each group WCC visit, the pediatrician will review group rules including confidentiality and the use of the session as a “safe space.” Any participant experiencing significant distress as a result of the discussion will be escorted from the room by one of the co-facilitators, and an on-site nurse manager or social worker at the SUD treatment program will be notified. In the case information is disclosed during group discussions about child abuse or neglect, intent to harm self, or intent to harm others, the pediatrician will follow standard reporting procedures as required by law.

### Plans for collection, laboratory evaluation, and storage of biological specimens for genetic or molecular analysis in this trial/future use {33}

N/A

## Statistical methods

### Statistical methods for primary and secondary outcomes {20a}

#### Quantitative data

Analyses will follow intent-to-treat principles, with participants analyzed according to randomized treatment assignment of the cluster in which they reside. Most analyses will use the individual participant as the unit of analysis, but because randomization is at the cluster level, model-based approaches that account for the correlation between individual participants within a cluster will be used.

Collected data will be summarized in tabular and graphic forms. Demographics and other study variables will be summarized by treatment groups. Mean (SD) or median (interquartile), as appropriate, will be used to describe numerical data, and frequency and percentage will be used to describe the distribution of categorical variables between treatment groups. Two-sample t-test, Mann–Whitney U test, chi-square test, and Fisher’s exact test will be used to compare the distribution of study variables between two-intervention groups as appropriate. Longitudinally collected data will be summarized by intervention groups and data collection time points.

Analysis of variance (ANOVA) and generalized linear and logistic regression models will be used to analyze outcomes measured at one time point, as appropriate. Trajectories of change for outcomes that are repeatedly measured over time will be examined using generalized linear mixed models (GLMMs) and linear, logistic, and negative binomial/Poisson regression models for continuous, binary, and count outcomes. Total scores and subscales from assessments will be used when applicable. The use of GLMM models will allow for an estimation of between-group differences in outcomes at each time point of measurement and will allow for an estimation of changes over time and time by group interactions while accounting for within-subject associations arising from the repeated measures. Clustering of participants will be accounted for in the GLMMs models by including cluster as a random or fixed effect and in the generalized models by using robust variance estimates. Potential covariates will be selected based on consideration of study arm balance and potential confounders for an outcome previously reported in the literature.

The analyses described above will be repeated for the secondary outcomes. We will construct GLMMs for repeated outcomes (e.g., mixed-effects linear regression models for continuous outcomes and mixed-effects logistic regression models for dichotomous outcomes) and ANOVA and generalized linear or logistic regression models for outcomes measured at one time point.

All analyses will be two-tailed with an overall level of significance of 0.05. The Benjamini–Hochberg method will be used for adjusting the level of significance for multiple testing. The statistical software SAS, version 9.4, and the latest version of R will be used for data analysis.

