**Methods:**

CHAMPS is a single-site 2-arm cluster randomized controlled trial. A total of 108 mother–child dyads will be enrolled into the study. Twenty-six clusters of approximately 4 mother-infant dyads each will be randomized 1:1 to one of two study arms (intervention or control). Clustering will be based on child’s month of birth. In the intervention arm, group well child care will be provided on-site at a maternal substance use disorder treatment program. Mother–child dyads in the control arm will receive individual well child care from one nearby pediatric primary care clinic. Dyads in both study arms will be followed prospectively for 18 months, and data will be compared between the two study arms. Primary outcomes include well child care quality and utilization, child health knowledge, and parenting quality.

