### Trial design {8}

This is a single-site cluster randomized controlled trial. One hundred eight pregnant and parenting women receiving treatment for OUD from one single opioid treatment program will be enrolled into the study. Twenty-six consecutive clusters—based on the one-month birth intervals of participants’ infants—of ~ 4 dyads will be randomized in a 1:1 ratio to one of two study arms. Thirteen clusters will be randomized to individual WCC (control group), and 13 birth clusters will be randomized to group WCC (intervention arm), with concealment of randomization from participants until after they have completed their initial enrollment study visit, or, for those who are pregnant at time of enrollment, immediately following delivery. Randomization by birth month was selected to ensure a close age range among infants receiving group WCC together in the intervention arm. Blocking or stratification was not used in the randomization. Dyads in both study arms will be followed prospectively for 18 months, and data will be compared between the two study arms. Primary outcomes include well child care quality and utilization, child health knowledge, and parenting quality. We hypothesize that at the end of the study period, participants in the intervention arm will have increased WCC engagement, knowledge about parenting, and maternal responsiveness compared to participants in the control arm.

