### Participant timeline {13}

### Sample size {14}

Assuming 150 births in the opioid treatment program over an 18-month recruitment period, > 90% rate of maternal legal guardianship at birth, 80% study participation rate, and equivalent group allocation (50%), we expect to enroll 108 participants (n = 54 per study arm) during the project period. A sample size of 54 per study arm will produce a two-sided 95% CI with a distance from the standardized difference in means between two arms to the limits that are equal to 0.38. Additionally, with a sample size of 54 per study arm, a two-sided test for the time-averaged difference between two means in a repeated measures design with a significance level of 0.05 will have 80% power to detect a standardized difference in means of 0.43 in a design with 4 repeated-measurements taken over the 18-month period and with between level correlations of 0.5. A sample size of 54 per study arm will give us 80% power to detect a standardized difference in means of 0.54 (effect size) between two arms using a two-sided two-sample t-test with a significance level of 0.05. Of note, we were unable to find reported data about the cluster effect of different birth months. However, we expect only a negligible cluster effect for birth-month, and so assumed no to negligible intra-cluster correlation coefficient (ICC; 0 to 0.05) to perform the power calculations, which is almost equivalent to performing simple random sampling. However, we preferred the design of cluster random sampling to simple random sampling to account for the effect of birth-month if there is any.

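### ANOVA is named for outcomes measured once, but the sentence that puts clustering into the models does not cover it, so the 18-month parenting-interaction score could be tested as if dyads were independent

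*Protocol article*

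**What the plan says.** The Trial design section states: "This is a single-site cluster randomized controlled trial". On allocation it says: "Thirteen clusters will be randomized to individual WCC (control group), and 13 birth clusters will be randomized to group WCC (intervention arm"). The abstract gives the cluster size: "Twenty-six clusters of approximately 4 mother-infant dyads each will be randomized 1:1 to one of two study arms".

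The Quantitative data subsection of the statistical methods {20a} contains four relevant statements.

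- It opens with a general rule: because clusters are randomized, model-based methods that allow for correlation within a cluster will be used.
- In the paragraph on summarizing data it says: "Two-sample t-test, Mann–Whitney U test, chi-square test, and Fisher’s exact test will be used to compare the distribution of study variables between two-intervention groups".
- For outcomes measured once it says: "Analysis of variance (ANOVA) and generalized linear and logistic regression models will be used to analyze outcomes measured at one time point, as appropriate".
- On how clustering enters the models it says: "Clustering of participants will be accounted for in the GLMMs models by including cluster as a random or fixed effect and in the generalized models", the latter through robust variance estimates.

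For secondary outcomes the text again names "ANOVA and generalized linear or logistic regression models for outcomes measured at one time point", with no clustering device attached.

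Under Outcomes {12}, several primary outcomes yield one value per dyad. KIPS is scored only at the 18-month visit. The visit count is a single total over 18 months, also classified as adequate or inadequate. KIDI is compared at 18 months and as change from baseline.

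**The concern.** A two-arm ANOVA on individual dyads is the pooled two-sample t-test. With 108 dyads it has 106 degrees of freedom and treats the dyads as independent. Only 26 units were randomized, so the comparison between arms has about 24 degrees of freedom. In the intervention arm the dyads of a cluster also attend their sessions together under one pediatrician, which gives a further reason to expect correlated outcomes.

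The general rule and the list of methods therefore do not fit together. The rule promises allowance for clustering, the implementing sentence provides it for two model families, and a third named method gets nothing. The qualifier that methods are chosen as appropriate leaves the analyst free to pick a test that ignores clusters or one that does not, with no rule fixed in advance. If ANOVA were run at dyad level on KIPS, the standard error would be too small whenever the ICC is positive. The Benjamini–Hochberg step would not repair p-values that are already too small.

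**Working it through.** **Inputs.** 108 dyads, 54 per arm, 26 clusters (13 per arm), two-sided 0.05, standardized difference 0.54 at 80% power, and ICC 0 to 0.05. All come from the Trial design and Sample size sections. Mean cluster size is m = 108/26 = 4.15.

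**1. Reproduce the plan's figure.** The Sample size section powers the single-time comparison "using a two-sided two-sample t-test with a significance level of 0.05". The detectable difference is (1.960 + 0.842) × √(2/54) = 0.539, which matches 0.54. With the t distribution on 106 df, power at 0.54 is 0.794. The figure reproduces with no design effect.

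**2. False-positive rate of a dyad-level ANOVA.** Design effect DE = 1 + (m − 1) × ICC. True two-sided level = 2 × [1 − Φ(1.96/√DE)]. The simulation used 13 clusters of 4 or 5 dyads per arm, 40,000 runs per ICC.

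| ICC | DE | 1.96/√DE | Level, formula | Level, simulated | Cluster-mean t-test, 24 df, simulated |
|---|---|---|---|---|---|
| 0 | 1.000 | 1.960 | 0.050 | 0.050 | 0.051 |
| 0.02 | 1.063 | 1.901 | 0.057 | 0.056 | 0.049 |
| 0.05 | 1.158 | 1.822 | 0.069 | 0.067 | 0.049 |

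A separate simulation with unequal cluster sizes gave 0.071 at ICC 0.05. If an ICC of 0.05 applies only in the group-care arm, the simulated level is 0.058.

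**3. Power of a valid test at 0.54.** At ICC 0, a test on 24 df has power 0.768, against 0.794 on 106 df: a loss of 2.6 points from degrees of freedom alone. At ICC 0.05 the effective size is 54/1.158 = 46.6 per arm, and power on 24 df is 0.71. Dyad-level ANOVA shows an apparent 0.79 in simulation. Part of that gap comes from its inflated level and is not real power.

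**4. Does the robust-variance route hold 5%?** Not without correction. In the same simulation, robust variance with a normal reference gave 0.074, 0.072 and 0.071 at ICC 0, 0.02 and 0.05. The reason is simple for equal cluster sizes: the uncorrected robust variance is 12/13 of the cluster-mean variance. Its cutoff of 1.96 therefore corresponds to 1.96 × √(12/13) = 1.883 on a t with 24 df, and P(|t| > 1.883) = 0.072. Multiplying the variance by 26/24 (= 13/12) and using the t reference on 24 df gives back the cluster-mean t-test, which holds about 5%.

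**The case against.** The opening rule comes before every listed method and can fairly be read as governing ANOVA too. ANOVA can carry cluster as a nested random factor or be run on cluster means, and the text never says one-way, dyad-level or 106 df. A condensed article may leave such detail to an analysis plan that is not shown. This stands to the extent that the article does not commit the trial to an unclustered analysis. It does not remove the point: the article does go into how clustering enters each model family, and in doing so passes over a method that it names twice.

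A reader might infer more than the document supports:

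- **That the t, Mann–Whitney, chi-square and Fisher tests are the outcome analyses.** They stand in the paragraph on summarizing data, before outcome analysis begins. They have no cluster adjustment and are not restricted to baseline, but nothing names them as a test of a primary outcome.
- **That every once-measured primary outcome is exposed.** Adequacy of visits is binary and goes to logistic regression with robust variance. The visit count can use a generalized model. KIDI is also measured at baseline, so a GLMM is available. KIPS is the clearest case, and even there a generalized linear model is named as an alternative.
- **That the t-test in the Sample size section shows how outcomes will be tested.** It is a power statement, not an analysis method.
- **That the false-positive rate reaches 9 to 10%.** That needs an ICC of 0.10, outside the protocol's range.

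**Conclusion.** The point holds as an inconsistency with a modest but real consequence. The plan promises analyses that allow for clustering, names ANOVA for outcomes measured once, and gives ANOVA no means of keeping the promise. If ANOVA were run on dyads, as the wording permits, its false-positive rate would be 5% at ICC 0 and about 7% at ICC 0.05, against about 5% for a cluster-level test on 24 df. These figures assume 13 clusters per arm of about 4 dyads, normally distributed scores, and the same ICC in both arms; with correlation in the group-care arm only, the upper figure is about 5.8%.

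The document does not support the stronger conclusion that the trial will ignore clustering in its primary analyses. Nor is the generalized-model route safe as it stands: uncorrected, it also sits near 7%, at every ICC in the range. The change is worth making because a primary outcome is affected and the correction is nearly free.

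**What to change.** In the Quantitative data subsection, make these changes in both the primary-outcome text and the sentence on secondary outcomes:

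1. Replace ANOVA for outcome comparisons with a method that carries birth-month cluster: a linear mixed model with arm fixed and cluster random, tested on about 24 between-cluster degrees of freedom, or a cluster-level analysis.
2. Where generalized models with robust variance are used, specify a small-sample correction to the variance and a t reference on about 24 degrees of freedom.
3. State that the two-sample tests in the summary paragraph are descriptive and will not be used for inference on outcomes.

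No new data are needed. Relative to a dyad-level ANOVA, interval half-widths grow by about 4% at ICC 0 (2.064/1.983 = 1.041) and about 12% at ICC 0.05 (1.041 × √1.158 = 1.120). Power at 0.54 is 77% at ICC 0 and 71% at ICC 0.05, against the planned 80%.

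### The plan lets cluster enter the mixed models as a fixed effect, which is aliased with study arm, so the promised arm difference at each visit cannot be estimated under that option

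*Protocol article*

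**What the plan says.** The protocol article, under Trial design {8}, states: "Thirteen clusters will be randomized to individual WCC (control group), and 13 birth clusters will be randomized to group WCC". The same section adds: "Blocking or stratification was not used in the randomization". Clusters are birth months, so all dyads in a cluster share one arm.

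Under Statistical methods {20a}, Quantitative data, repeated outcomes go to generalized linear mixed models. The text says these models will estimate the between-arm difference at each measurement time, change over time, and the time-by-arm interaction. Clustering is handled there "by including cluster as a random or fixed effect and in the generalized models by using robust variance estimates". The first half of that wording governs the mixed models. The second half governs the generalized models used for outcomes measured once.

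Under Outcomes {12}, the PHDS is collected at 6, 12 and 18 months, and the mean of each of its five components is to be compared between arms at every one of those visits. This is part of a primary outcome.

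**The concern.** In a parallel cluster-randomized design, arm is a property of the cluster. A model that gives every cluster its own fixed parameter has already absorbed everything that differs between clusters, including arm. The plan offers this model as an equal alternative to a random cluster effect, in the same paragraph that promises arm differences visit by visit.

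For the PHDS, the part that survives does not replace the part that is lost. The survey has no baseline measurement, so arm-by-time contrasts describe only change after month 6. For mothers enrolled in pregnancy, group visits begin with the 1-month visit (Intervention description {11a}). A benefit already present at 6 months and then sustained would not show in those contrasts.

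The secondary outcomes are to be analyzed in the same way. The same problem therefore reaches those compared at several visits, such as the urine drug screens.

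**Working it through.** **Inputs.** 26 clusters of about 4 dyads (abstract, Methods); 13 clusters per arm, no stratification (Trial design {8}); 108 dyads, 54 per arm, ICC 0 to 0.05 (Sample size {14}); two-sided level 0.05 (Quantitative data).

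**The plan's own figures.** The plan gives no figure on the fixed-effect option itself. Its sample-size figures reproduce at ICC 0:
- n per arm = 2(1.96 + 0.8416)²/0.54² = 53.8, so 54.
- Detectable repeated-measures difference = 2.8016 × √(2 × 0.625/54) = 0.426, against 0.43 stated, where 0.625 = (1 + 3 × 0.5)/4.
- Half-width of the confidence interval = 1.96 × √(2/54) = 0.377, against 0.38 stated.

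**Aliasing at one time point.** Number the control clusters 1 to 13 and the intervention clusters 14 to 26, with D_k the indicator of cluster k. For every dyad, arm = D_14 + … + D_26. Adding any constant c to the arm coefficient and subtracting c from those 13 cluster coefficients leaves every fitted value unchanged. Numerically:
- intercept + 25 cluster indicators: rank 26;
- the same + arm (27 columns): rank still 26.

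The argument concerns the linear predictor, so it holds for the logistic and count models too. A random participant effect does not change it.

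**Aliasing with repeated measures, four time points.**
- intercept + 3 time + 25 cluster indicators: rank 29;
- adding arm: rank 29;
- adding arm-by-time: rank 32.

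Arm adds nothing, and the three arm-by-time columns add three. The arm difference at visit t is β + γ_t. Since β is not estimable, no visit-specific difference is; only the contrasts among visits are. With the three PHDS visits, the same counting leaves two contrasts.

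**What software may print.** If a program drops one aliased cluster indicator and carries on, the column labelled arm can still receive a coefficient. Computed for a coding with one reference cluster left in each arm, that coefficient has weight −1 on one control cluster, +1 on one intervention cluster and 0 on the other 24. It compares about 4 dyads with about 4, not 13 clusters with 13.

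**Secondary check, robust variance for outcomes measured once.** Null simulation, 20,000 trials per scenario, 26 clusters split 13:13, mean size about 108/26 = 4.15 (sizes 4–5, 3–5 or Poisson), ICC 0 and 0.05, continuous outcome and binary outcome at 50%, no covariates:

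| Test at nominal 5% | Rejection |
|---|---|
| Uncorrected sandwich, z | 6.7% to 7.7% |
| Uncorrected sandwich, t on 24 df | 5.3% to 6.3% |
| Finite-sample factor (CR1), t on 24 df | 4.7% to 5.7% |

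A second run with Poisson sizes and prevalence from 20% to 50% (15,000 trials per scenario) gave 7.5% to 8.0% for the uncorrected z-test.

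**The case against.** The strongest reply is that the option is narrow and a valid alternative stands beside it. This is largely right. A random cluster effect is named first and works. The fixed-effect choice applies only to the mixed models, so visit count, adequacy of care and the parenting-interaction score (KIPS) at 18 months are untouched. Time-by-arm interactions are themselves treatment effects that the plan names, and the planned comparison of change in the parenting-knowledge score (KIDI) from baseline survives. A reader might infer that no treatment effect at all can be estimated; the documents do not support that.

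A second reply is that cluster can be coded as nested in arm, and the cluster effects averaged within arm. That does produce a number, but only under an added constraint that the plan does not state, and its standard error omits between-cluster variation. At ICC 0.05 and 4 dyads, the variance of a cluster mean is 0.05 + 0.95/4 = 0.2875 of the total. The fixed-effect calculation sees only 0.2375, a ratio of 0.83. It would not do what the sentence is there to do.

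A reader might also infer that the plan prescribes an uncorrected robust variance, or tests that ignore clusters. Neither is stated. The text names robust variance without an estimator or reference distribution, and an analysis plan not shown may supply both. The t, Mann–Whitney, chi-square and Fisher tests sit in the paragraph on descriptive summaries, in a section that opens by committing to models that respect within-cluster correlation. The sentence "Analysis of variance (ANOVA) and generalized linear and logistic regression models will be used to analyze outcomes measured at one time point" is loosely worded about ANOVA, but it is not a plan to ignore clusters.

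What the reply cannot remove is that the protocol names the fixed effect as a permitted choice. This is stated text, not a detail left open.

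**Conclusion.** The point holds in this form: under the fixed-effect option the arm main effect and every visit-specific arm difference are not estimable (rank 26 of 27 columns), so the section contradicts its own promise. Among the primary outcomes it bears clearly on the five PHDS component scores at 6, 12 and 18 months. This is an algebraic result. It rests only on each cluster lying wholly in one arm, not on the ICC, cluster size or any distribution.

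The robust-variance remark is a suggestion, not an error found. The excess of roughly 2 to 3 percentage points depends on no correction being used, a z reference, normal cluster effects, no covariates and no dropout. Against the plan's rule "All analyses will be two-tailed with an overall level of significance of 0.05" it is modest, and a finite-sample correction with t on 24 df largely removes it.

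**What to change.** In Quantitative data, delete the words *or fixed*. State that the mixed models carry a random cluster effect with participant nested in cluster, preferably with a small-sample degrees-of-freedom method such as Kenward–Roger for the linear models.

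As a secondary suggestion, have the analysis plan name a small-sample correction for the robust variance and a t reference on 24 df (26 clusters minus 2 arms), and say that any ANOVA of a single-time outcome also accounts for cluster.

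The cost is one sentence of wording and standard options in SAS or R. No data collection changes. Where a correction would not otherwise have been used, confidence intervals become slightly wider.
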